### Outcome Measures

Our primary effectiveness outcome of HIV testing is measured using self-report and objective proof (eg, screenshot or photo of HIV testing results uploaded to REDCap, our survey software) while secondary effectiveness outcomes (eg, PrEP uptake and STI testing) are measured via self-report only. We remind all adolescents across study arms at multiple time points (consent, ID verification call, and active or control arm messages related to HIV testing, and boosters) to retain evidence of testing. As some may not notify us immediately, each follow-up survey asks for testing experiences since the prior assessment. Those who report being tested are prompted to securely upload evidence of their HIV or STI test via a participant-specific REDCap link in line with procedures from prior work [68,69]. If any participants report testing positive for HIV or STIs, a staff member will promptly contact the participant and link them to care.

#### Quantitative Analysis

We hypothesize that participants in the SHER intervention and control groups will differ in whether they are tested for HIV during the study and that HIV prevention, testing, and treatment information, motivation, and behavioral skills will mediate these effects (Table 1). Our secondary outcomes will include PrEP initiation; discussion with providers about HIV, STI testing, and PrEP; and frequency of receptive or insertive condomless sex and STI testing.

We will assess the experimental and control groups’ similarities at baseline. Variables that differ significantly will be covariates in adjusted outcome analyses, along with variables correlated with the outcome (eg, age), as well as covariates associated with missingness in order to address differences in attrition [70-74]. The primary outcome will be analyzed using a generalized linear mixed effects model that assumes a binomial distribution and logit link. The generalized linear mixed effects model will incorporate data from baseline, 3-month, and 6-month follow-ups and account for both fixed and random effects over time. Residual diagnostics will be used to evaluate model fit, including the possibility of overdispersion. We will report study arm coefficients as log odds ratios and report odds ratio point estimates, SEs, and 95% CIs. The test of the treatment effect will be 2-sided Wald tests that control the type I error rate at α=.05. Missingness will be addressed using either full information maximum likelihood (if missingness is less than 25% as anticipated) or multiple imputation (if missingness is greater than 25%) [75].

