### RCT Launch (June 2024-February 2025)

#### Overview

The recruitment, enrollment, and study time points across both arms of the study are outlined in Figure 3. The RCT was launched in June 2024, and initial eligibility criteria were (1) male gender identity or male sex at birth, (2) ever had anal sex with a partner assigned male at birth, (3) identify as a sexual or gender minority or are questioning their sexuality, (4) aged 13‐18 years, (5) read in English at a 6th grade level, (6) never received an HIV or STI test, (7) HIV negative or unknown status, (8) own a cell phone with an unlimited MMS plan and plan to have the same number during the study, (9) can provide informed consent, as shown on a capacity to consent assessment [45], and (10) live in the United States or US territories. Like the YAC, participants initially were recruited predominantly via social media platforms, where they viewed advertisements that directed them to a study information page, followed by a brief online screener and a required identity verification call. Informed consent and assent are completed online by the participant, followed by a video chat with study staff to answer questions and/or address concerns about the study prior to enrollment. All personal information from potential and enrolled participants is collected remotely and stored in REDCap (Research Electronic Data Capture; Vanderbilt University) and private university servers.

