#### Changes to Sample Size (August 2025-March 2026)

In summer 2025, although the enrollment rate increased, it was not enough to compensate for the time lost in the earlier months of the RCT, and the team was experiencing several additional challenges. First, there was uncertainty about whether the project would continue to be funded by NIH due to changes in federal funding priorities, and the grant budget had been reduced substantially. Furthermore, RCT and Aim 3 activities were occurring simultaneously due to the recruitment delays, requiring study staff to manage competing priorities. In addition, the longer recruitment lasted, the more costs would be incurred for advertising and retention. These factors led the investigative team to explore the feasibility of reducing the sample size to conserve resources and ensure completion of the trial before the end of the grant period.

Power calculations were performed using nominal type I error rates (α=.05) and assumed a 1:1 allocation to each study arm and identical arm-specific retention rates. The assumed HIV testing rate for control participants at the final time point was 28% based on previous findings from the G2G pilot study [26]. The original sample size proposed in the grant (n=360) was chosen to power comparisons at the end of the trial. Assuming 80% retention, the study would be 81% powered to detect a small to medium intervention effect for self-reported or objective HIV testing. Revised power calculations were conducted in August 2025 by a biostatistician. It was concluded that, assuming study endpoint retention rates of 90% or higher, the study’s target sample size could be reduced from 360 to 310 and maintain the 80% power to detect differences between the intervention and control groups at the same magnitude that was targeted in the original power analysis. At the time of these analyses, study retention was at or near 90% and, in March 2026, exceeded 90%. The sample size reduction and expanded inclusion criteria will likely limit the ability to conduct adequately powered subgroup analyses, so those analyses will be treated as exploratory. However, maintaining the higher targeted retention rate should allow for mediation analysis at similar power levels as the originally targeted sample size. Assuming these recruitment rates hold, we anticipate completing recruitment by June 2026 and retention efforts by January 2027.

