#### Pre- and Postlaunch Protocol Modifications

In summary, our study originally aimed to enroll 360 participants between the ages of 13 and 18 years who were assigned male at birth or had a masculine gender identity, had not previously obtained an HIV test, and had engaged in penetrative sex with a partner assigned male at birth. In March 2025, we expanded the criteria to include 19-year-olds, individuals assigned female at birth who were at elevated risk for HIV, and those who had previously obtained an HIV test but at the time of enrollment were eligible for another HIV test. Despite implementation of multiple recruitment strategies, recruitment continued to progress slower than anticipated. In 2026, the study team therefore reduced the sample size to 310, having determined that statistical power would be retained provided retention rates remained at or above 90%, which was highly likely based on interim retention rates. All modifications were approved by the IRB and NIH prior to implementation, and ClinicalTrials.gov was updated accordingly.

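### The primary mixed model appears to take baseline HIV testing as a response and names no treatment contrast; if the test were arm-by-time, its power would be very low

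*Protocol article*

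**What the plan says.** In Quantitative Analysis the primary outcome is analysed with a binomial, logit-link mixed model that "will incorporate data from baseline, 3-month, and 6-month follow-ups and account for both fixed and random effects over time". Covariates are dealt with in a separate sentence, which does not mention baseline testing. On reporting: "We will report study arm coefficients as log odds ratios and report odds ratio point estimates, SEs, and 95% CIs". On testing: "The test of the treatment effect will be 2-sided Wald tests that control the type I error rate at α=.05". No arm-by-time term is mentioned, and no contrast is identified as the treatment effect.

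Table 1 (Assessment) collects HIV testing at baseline under the same three-month look-back definition as at follow-up. The launch eligibility criteria (RCT Launch, Overview) required that participants had "never received an HIV or STI test". The criteria were later widened to admit "those who had previously obtained an HIV test but at the time of enrollment were eligible for another HIV test" (Pre- and Postlaunch Protocol Modifications). The Randomization section then added ever/never testing history as a stratification variable within the minimisation scheme.

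The hypothesis, in both the Introduction and Quantitative Analysis, concerns testing during the study. The sample size was set for an end-of-trial comparison (Changes to Sample Size).

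**The concern.** Baseline stands in the list of model time points next to the two follow-ups, so the natural reading is that it is a response row. For a never-tested participant that row is zero by definition. For a previously tested participant who was due another test, a test in the past three months is probably uncommon: the shortest screening interval cited in the Introduction is 3 to 6 months, and those taking PrEP were not admitted by this route. The article gives neither the share never tested nor a minimum interval since the last test, so this is likely rather than known.

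A nearly empty baseline matters if the treatment effect is read as change from baseline. The interaction then subtracts a baseline log odds ratio that is barely estimable, or not estimable at all, and Wald tests behave badly under such separation. With baseline as the reference time, the arm coefficient in that model is only the baseline difference between arms, which is null by randomisation. At stake are the power of the primary test and the meaning of the reported odds ratio.

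**Working it through.** **1. The plan's own power figures.** Inputs from Changes to Sample Size: two-sided α = 0.05, 1:1 allocation, control rate 28%, 360 at 80% retention with 81% power, then 310 at 90% retention with 80% power. The effect is given in words only, so it is solved from the first power figure.

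Power = Φ{[Δ√n − 1.96√(2p̄(1−p̄))] / √(p₁(1−p₁)+p₂(1−p₂))}, where n is the number per arm.

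- 360 × 0.8 = 288, so n = 144. With p₁ = 0.28, p₂ = 0.44, p̄ = 0.36: (0.16 × 12 − 1.96 × 0.679)/0.669 = 0.88, giving 81%. The implied odds ratio is (0.44/0.56)/(0.28/0.72) = 2.02.
- 310 × 0.9 = 279, so n = 139.5: (0.16 × 11.81 − 1.96 × 0.679)/0.669 = 0.84, giving 79.8%.

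The two stated figures agree with each other. Because the effect was solved from the first, this does not independently confirm the 81%.

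**2. Why the arm-by-time contrast is fragile.** The 6-month interaction is (arm log OR at 6 months) − (arm log OR at baseline). Ignoring the random effect, the baseline log OR has variance of about 1/e + 1/e + 1/(140−e) + 1/(140−e), with e events per arm.

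- 42 events (e = 21): 0.112, SE 0.33.
- 8 events (e = 4): 0.515, SE 0.72.
- 0 events: infinite.

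**3. Simulation.** Random-intercept logistic model, 140 per arm, two follow-up visits calibrated to 28% vs 44% ever tested, intercept SD 1.5, categorical time, 450 trials per scenario (Monte Carlo error about 2 points). Expected baseline events = 280 × (1 − share never tested) × rate among the previously tested.

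| Never tested | Baseline rate in the rest | Baseline events | Interaction at 6 months: SE, power | Joint 2-df interaction: power | Main effect: log OR, power | Arms equal at baseline: power |
|---|---|---|---|---|---|---|
| 100% | – | 0 | about 2000, 0.7% | 2.4% | 0.90, 83% | 83% |
| 90% | 10% | 2.8 | 1.47, 1.1% | 2.0% | 0.84, 83% | 84% |
| 70% | 10% | 8.4 | 0.85, 15% | 9% | 0.76, 81% | 86% |
| 70% | 30% | 25 | 0.55, 31% | 26% | 0.62, 77% | 87% |
| 50% | 30% | 42 | 0.47, 35% | 33% | 0.54, 74% | 88% |

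Follow-up visits only: log OR 0.90, SE 0.315, power 83%.

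Hand check from the median estimates: follow-up only, 0.903/0.315 = 2.87, Φ(2.87 − 1.96) = 82%; interaction with 42 events, 0.724/0.472 = 1.53, Φ(1.53 − 1.96) = 33%. Both are close to the simulated values.

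**4. Sensitivity.** An intercept SD of 1.0 gave the same pattern in all scenarios. An SD of 2.5 did so in the first three, the only ones completed. With linear time and an all-zero baseline, the arm-by-slope test has 1% power, while the main effect shrinks to 0.79 with power of 84%.

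**The case against.** The strongest reply is that the article never names an arm-by-time test. It speaks of arm coefficients and of a test of the treatment effect, and a condensed article may leave the contrast to an analysis plan that is not shown. Saying that a model incorporates baseline data could even mean baseline as a covariate. This stands. A reader might infer that the planned primary test is arm-by-time and will fail; the document does not support that.

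A reader might also infer that the forced zeros dilute the arm coefficient. They do not. With categorical time an all-zero baseline carries no information on arm, and the main-effect result equals the follow-up-only result. Dilution needs actual baseline positives, which is the opposite condition from the one that breaks the interaction test. The two harms therefore do not add up.

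Part of the gap between 35% and 83% also comes from testing one visit rather than two: a plain comparison at one follow-up visit has roughly 60% to 70% power under the same calibration. The joint 2-df interaction test uses both visits, however, and does no better than the single-visit one.

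The reply does not remove the point that baseline is listed as a model time point, that covariates are handled elsewhere, and that pre-randomisation testing is no part of the stated hypothesis. Leaving the contrast open until data are seen also allows a choice between tests of very different power.

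**Conclusion.** The point holds as a conditional one.

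- **If arm-by-time against baseline:** the planned Wald test has about 1% power with an empty baseline and at most about 35% in the scenarios run, against about 83% from follow-up data. The reported arm coefficient would be the baseline difference.
- **If arm main effect only:** structural zeros do no material harm. Real baseline positives pull the log odds ratio from 0.90 to 0.84 with about 3 events, a 7% reduction, and to 0.54 with about 42, a 40% reduction. Power falls from 83% to 74% at worst.

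An unconstrained baseline response gained no material power in any scenario. The sizes rest on assumptions that the article does not supply: 28% vs 44% taken as ever tested over two follow-up visits, 50% to 100% never tested, a 10% to 30% baseline rate among the previously tested, and the intercept SD. This is a free improvement that depends on model form, not a demonstrated failure of a stated test.

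**What to change.** In Quantitative Analysis, state three things:

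1. The primary response is HIV testing after randomisation only.
2. Baseline testing history (ever/never) enters as a covariate. It is already a minimisation factor, so it is already collected.
3. The arm contrast on follow-up data is the treatment effect, and its odds ratio is the one reported.

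An acceptable alternative keeps baseline as a response with the arms constrained equal there; in the simulations this had 83% to 88% power.

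The cost is one or two sentences, with no new data and no participant burden. The wording should be settled before outcome data are examined by arm.

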#### Qualitative Analysis

Postintervention interview transcripts will be uploaded to Dedoose [76,77]. Directed content analysis will identify and summarize intervention acceptability and completion barriers or facilitators [78-81]. Codes will be iteratively refined and applied to the data until reliability reaches kappa 80% [82].

#### Data Security and Participant Safety

A DSMB composed of 3 independent experts was assembled to ensure participant safety, data integrity, and ethical conduct. The first meeting occurred in April 2024 prior to the start of the trial. The board meets every 6 months, with the final meeting planned for after data collection concludes. During meetings there is (1) an open session in which the study team reviews the progress of the study and answers questions from members of the DSMB; (2) a closed session involving DSMB members (if determined necessary) where the study statistician discusses quantitative outcomes and answers questions; and, if requested, (3) a final session involving DSMB members only to discuss study progress and outcome results, develop recommendations, and take votes as necessary. Each meeting is led by a chair, which alternates every meeting and is responsible for issuing a final recommendation to continue, modify, or end the study.

Participant data will be coded with randomly generated identifier codes; responses will never be linked to a participant’s name, email address, phone number, or any other identification information. All data presented will be done in aggregate without any personal identifiers. All survey data will be stored in REDCap and housed on Northwestern University computers and servers. Participants in interview portions of the study participate in a Zoom interview or telephone interview if they are unable to use Zoom. Audio is recorded via Zoom or digital audio recorder and transferred to secure Northwestern servers immediately after the interview. Following this, audio files are deleted from local devices. Interview audio is uploaded to a secure online transcription service. All interview data are deidentified by research staff prior to entry into a cloud-based qualitative data analysis software. Deidentified data are stored indefinitely on secure shared drives on university servers.

During the trial, participants provide their phone numbers and receive automated SMS text messaging and MMS messages from a dedicated Northwestern server that delivers the intervention. Paradata such as engagement with SMS text messaging (eg, replying to question prompts sent via text) is transmitted back to university servers and exported into Excel (Microsoft) files for analysis. Group SMS text messages are routed through the server and delivered to participants. This avoids participants having to disclose phone numbers with others in their group, enables recording of SMS text messaging for analysis, and allows the study team to monitor group texts for inappropriate or bullying behavior.

### Approach for Aim 3

Aim 3 activities were focused on identifying expert- and adolescent-recommended strategies for reaching and engaging SGM youth in digital sexual health interventions. Specifically, this aim identified, specified, and prioritized effective strategies for increasing a digital health intervention’s reach, defined as adolescents who are aware of the digital intervention and decide to participate, and engagement*,* defined as adolescents who continue to use or participate in the digital intervention. The overarching goal was to provide any individual or organization who aims to include SGM adolescents in digital outreach, programming, or interventions (eg, researchers, industry partners, and community organizations) with expert guidance that can enhance their ability to reach and engage these adolescents.

To achieve this goal, concurrent with Aim 2 activities, we recruited 18 individuals in the United States who had expertise in SGM health, adolescent health, HIV prevention, sexual health, digital health interventions, digital marketing, or other areas relevant to SHER. Experts were recruited via professional networks, snowball referrals, and cold-emailing different organizations identified through social media and internet-based searches. This purposive sampling approach was taken to ensure that the panelists reflected the appropriate areas of expertise to offer comprehensive and trustworthy recommendations for reaching and engaging SGM adolescents in a variety of settings.

This aim used a pragmatic sequential mixed methods process modeled after the methods used to develop the Expert Recommendations for Implementing Change, a taxonomy of expert-identified implementation strategies [83,84]. The process consisted of 3 phases, including identifying strategies to reach adolescents and determinants of these strategies, rating these strategies and determinants to understand how experts prioritize them, and connecting and building upon findings from the first 2 phases via discussion and consensus. Experts were compensated US $1000 for participating in several activities over approximately 6 months, including 2 surveys, a focus group, and a 4-hour-long panel meeting.

### Identifying Determinants and Implementation Strategies for Reaching and Engaging Adolescents

This phase consisted of a series of 90-minute focus groups conducted via Zoom [85] with 3‐5 expert panel members each in April-May 2025. Focus groups were recorded and transcribed. Prior to each focus group, each expert completed a brief demographic survey that included 3 open-ended questions, “What are some of the most successful ways you have reached and engaged SGM teens in your programs? These could be different ways for reaching teens vs engaging teens in programs” “What has gotten in the way of successfully reaching and engaging SGM teens in your program?” and “What has made it easier to successfully reach and engage SGM teens in your program*?*” These survey responses were used by the research team to identify common and unique themes across panelists to guide the focus group discussion.

During the focus groups, experts were asked to discuss these practices (ie, strategies) in their respective organizations for reaching and engaging SGM adolescents. The research team prompted panelists to specify the actors who do the strategy, the specific actions taken, the temporality of when the strategy is used, and the dosage (frequency and time) of each strategy [86]. This prompting focused on identifying the rationale or justification for using a specific strategy, with a focus on identifying specific barriers and facilitators to reaching and engaging SGM adolescents that would be addressed by the strategy. The research team then engaged in rapid qualitative content analysis of the focus group transcripts and facilitator notes to generate a preliminary list of strategies corresponding to barriers and facilitators [78-81].

### Rating Reach and Engagement Strategies and Determinants to Inform Prioritization

A comprehensive list of all reach and engagement strategies, barriers, and facilitators identified during the focus groups was prepared by the research team following consolidation of conceptually similar items. These lists were presented to the experts through an online survey sent in July 2025, which asked them to rate both the feasibility and importance of each strategy using a 10-point Likert scale (1: least-10: most). Determinants were assigned as a barrier or facilitator based on information and context from the focus groups. Panelists were asked to rate each determinant on a 3-point scale based on their respective influence on reach and engagement of SGM adolescents ([1] small impact, [2] medium impact, and [3] strong impact) [87]. Open-ended questions for reach and engagement strategies and determinants enabled experts to provide additional context for their ratings. Descriptive statistics were conducted to summarize the average feasibility and importance of each strategy and the relative impact of the barriers and facilitators. The open-ended responses were analyzed using rapid qualitative content analysis [78-81]. The research team used the survey data to generate the strategies and determinants sections of an implementation research logic model, which indicated the relationships between determinants and strategies [88-90].

